## 7.2 Relationship

Definite – The AE *is clearly related* to the study treatment.

Probable – The AE *is likely related* to the study treatment.

Possible – The AE *may be related* to the study treatment.

Unlikely – The AE *is doubtfully related* to the study treatment.

Unrelated – The AE *is clearly NOT related* to the study treatment.

## 7.3 Expectedness

Unexpected adverse event: An adverse event, which varies in nature, intensity or frequency from information on the investigational drug/agent provided in the Investigator's Brochure, package insert or safety reports. Any adverse event that is not included in the informed consent is considered "unexpected".

Expected (known) adverse event: An adverse event, which has been reported in the Investigator's Brochure. An adverse event is considered "expected", only if it is included in the informed consent document as a risk.

## 7.4 Handling of Expedited Safety Reports

In accordance with local regulations, the IND Sponsor ([name]) will notify investigators of all SAEs that are unexpected (ie, not previously described in the package insert or Investigator Brochure), and definitely, probably, or possibly related to Helixor® M. This notification will be in the form of an expedited safety report (ESR) that is to be faxed to the investigators and the study coordinators within 24 hours of notification of the event. Upon receiving such notices, the investigator must review and retain the notice with the Investigator's Brochure and where required by local regulations, the investigator will submit the ESR to the appropriate IRB. The investigator and IRB will determine if the informed consent requires revision. The investigator should also comply with the IRB

procedures for reporting any other safety information. Where required, submission of ESRs by the investigator to Health Authorities should be handled according to local regulations.

## 7.5 Reporting

### 7.5.1 General

All adverse events (both expected and unexpected) will be captured on the appropriate study-specific case report forms (CRFs). In addition, all serious adverse events, regardless of causality to study drug, will be reported promptly to the IND Sponsor [name] [contact], email: [[contact]](mailto:[contact])) within 24 hours of recognition of the adverse event using the form found in **Appendix B**. If this falls on a weekend or holiday, an email notification is acceptable but must be followed by an SAE reporting form on the next business day.

### 7.5.2 Institutional Review Board (IRB)

All serious adverse events will be reported to the Institutional Review Board (IRB) per institutional guidelines. Follow-up information will be submitted to the IRB per institutional guidelines as soon as relevant information is available.

### 7.5.3 Food and Drug Administration (FDA)

#### 7.5.3.1 Expedited IND Safety Reports:

##### *7 Calendar-Day Telephone or Fax Report:*

The IND Sponsor is required to notify the FDA of any fatal or life-threatening adverse event that is unexpected and assessed by the investigator to be possibly related to the investigational agent. Such reports are to be telephoned or faxed [contact]) to the FDA within 7 calendar days of first learning of the event. Follow-up information will be submitted to the FDA as soon as relevant information is available.

##### *15 Calendar-Day Written Report:*

The IND Sponsor is required to notify the FDA of any serious adverse event that is unexpected and possibly related to the investigational agent in a written IND Safety Report.

Written IND Safety Reports should include an Analysis of Similar Events in accordance with regulation 21 CFR § 312.32. All safety reports previously filed with the IND concerning similar events should be analyzed. The new report should contain comments on the significance of the new event in light of the previous, similar reports.

Written IND safety reports with Analysis of Similar Events are to be submitted to the FDA within 15 calendar days of first learning of the event. Follow-up information will be submitted to the FDA as soon as relevant information is available.

#### 7.5.3.2 IND Annual Reports

In accordance with the regulation 21 CFR § 312.33, the IND Sponsor shall within 60 days of the anniversary date that the IND went into effect submit a brief report of the adverse events and progress of the investigation. Please refer to Code of Federal Regulations, 21 CFR § 312.33 for a list of the elements required for the annual report. All IND annual reports will be submitted to the FDA by the IND Sponsor.

### 7.6 Possible Adverse Events

Adverse drug reactions to Helixor IV infusion include urticaria, generalized or localized itching, dyspnea/bronchospasm, quinke's edema, activation of former SC injection site reactions, erythema with or without swelling, fever, exanthema, anaphylaxis, chills, flu-like symptoms, abdominal pain, joint swelling, paresthesia, deterioration of pre-existing bone pain. Additional reported side effects include: fatigue, headache, and infusion site inflammation.

## 8. PHARMACEUTICAL INFORMATION

A list of the adverse events and potential risks associated with Helixor® M can be found in **Section 7.6**.

Detailed instructions regarding the storage, preparation, and administration of Helixor® M can be found in the pharmacy manual.

### 8.1 Mode of Action

Several biologically active substances are found in mistletoe extracts: lectins, viscotoxins, peptides, amino acids, flavonoides, oligo and polysaccharides, and other substances in low concentrations. Mistletoe extract has two mechanisms of action, tumor cytotoxicity and immunomodulation. The cytotoxic effects of mistletoe extract are a result of protein synthesis interference, cell cycle inhibition, and inducing apoptosis. The immunomodulatory properties of mistletoe extract work through increasing white blood cell numbers, as well as stimulating the production of immune enhancing cytokines (IL-1, IL-6, TNF- $\alpha$ ). Lastly, mistletoe extract has been shown to have anti-angiogenic properties. In Europe, Helixor® M is used as an anthroposophic medicine in the treatment of malignant and non-malignant tumors, malignant disorders with accompanying impairment of the hematopoietic organs, stimulation of bone marrow activity, reducing the risk of tumor recurrence, and diagnosed pre-cancerous disorders.

### 8.2 Product description

1 ml injection solution Helixor® M 50 mg contain: 1,006 mg aqueous extract (1:20) from 50 mg fresh herbal substance of apple tree mistletoe. Helixor® M 100 mg has the same strength but is filled in 2-ml ampoules. Other constituents include: Sodium chloride for isotonization, sodium hydroxide for pH adjustment. Water for injection is added as vehicle for the medicinal product formulation.

Sterile injection solution filled into burn-up ampoules with single point cut (DIN ISO 9187) made of colorless glass type I. Supplied as Original Packs (OPs) each with 8 ampoules Helixor® M or as Great Packs (GPs) each with 50 ampoules Helixor® M.

### 8.3 Storage and Labeling

The product should be stored in the refrigerator ( $5^{\circ}\text{C} \pm 3^{\circ}\text{C}$ ) in the original package to protect the contents from light. The ampoules should not be used if they have been previously opened or exposed to ultraviolet light.

### 8.4 Stability

Helixor® M has a shelf life of 2 years; the expiration date is printed on each ampoule and box. The administration of Helixor® M must be completed within 24 hours of preparation. If not used immediately, the infusion solution may be stored under refrigeration conditions ( $2^{\circ}\text{C}$ - $8^{\circ}\text{C}$ ,  $36^{\circ}\text{F}$ - $46^{\circ}\text{F}$ ) for up to 20 hours, and a maximum of 4 hours of the total 24 hours can be at room temperature ( $20^{\circ}\text{C}$ - $25^{\circ}\text{C}$ ,  $68^{\circ}\text{F}$ - $77^{\circ}\text{F}$ ). The maximum 4-hour period under room temperature includes the product administration period. The IV bag should be allowed to equilibrate to room temperature prior to subsequent use.

### 8.5 Preparation and Administration

Helixor® M should be diluted with 0.9% Sodium Chloride Injection, USP using the following Reconstitution schema:

| Dose Group (mg) | Investigational Product | 0.9% NaCl |
|-----------------|-------------------------|-----------|
| 50              | 1 ampule (1ml)          | 249ml     |
| 150             | 1.5 ampules (3ml)       | 247ml     |
| 300             | 3 ampules (6ml)         | 244ml     |
| 600             | 6 ampules (12ml)        | 238ml     |
| 900             | 9 ampules (18ml)        | 232ml     |
| 1200            | 12 ampules (24ml)       | 226ml     |
| 1500            | 15 ampules (30ml)       | 220ml     |
| 1800            | 18 ampules (36ml)       | 214ml     |
| 2000            | 20 ampules (40ml)       | 210ml     |

The administration of Helixor® M at room temperature ( $20^{\circ}\text{C}$ - $25^{\circ}\text{C}$ ,  $68^{\circ}\text{F}$ - $77^{\circ}\text{F}$ ) must be completed within 4 hours. Care must be taken to assure sterility of the prepared solution as the product does not contain any anti-microbial preservative or bacteriostatic agent. In this study, Helixor® M will be administered intravenously three times per week. To avoid pseudo-allergic reaction the optimum drip speed should not be exceed 26 drops per minute, corresponding to the infusion time of approximately 3 hours. Infusion times are approximate (+/- 15min) and may need to be adjusted based on patient tolerability. At the end of the infusion, flush the line with a sufficient quantity of normal saline.

## **8.6 Patient Care Implications**

There is a possible risk of anaphylaxis and Helixor® M should be administered in a setting where emergency treatment is available. Administration should be immediately discontinued and the appropriate therapy instituted if there is a serious allergic reaction. The patient must be observed in the clinic for at least 30 minutes after the lead in dose and the first dose of the assigned dose level. Acute reactions (allergic or allergic-like reactions such as generalized itching, hives, rash, swelling of the face or throat, chills, difficulty breathing, shock or spasm of the airways) will be managed using standard therapy for acute drug reactions as per institutional standard of care and reported to the sponsor. If a grade 1 or 2 hypersensitivity reaction is suspected, this must be discussed with the IND sponsor and principal investigator before the patient is given another dose of Helixor® M. Patients developing grade 3 or 4 hypersensitivity will not receive another dose of Helixor® M.

Interactions of mistletoe products with other drugs are not known. In two different studies, neither induction nor inhibition of cytochrome P450 isoenzymes could be detected for Helixor® M.

## **8.7 Returns and Reconciliation**

The investigator is responsible for keeping accurate records of the clinical supplies received from Helixor or designee, the amount dispensed to, and returned by the subjects and the amount remaining at the conclusion of the trial.

Upon completion or termination of the study, all unused and/or partially used investigational product will be destroyed at the site per institutional policy. It is the Investigator's responsibility to arrange for disposal of all empty containers, provided that procedures for proper disposal have been established according to applicable federal, state, local and institutional guidelines and procedures, and provided that appropriate records of disposal are kept.

## **9. CORRELATIVE/SPECIAL STUDIES**

### **9.1 Peripheral Blood Mononuclear Cells (PBMC) Studies**

Baseline and post-treatment PBMC will be collected to monitor peripheral immunologic changes in response to therapy. The peripheral blood will be obtained from each research participant at periodic protocol-specified intervals for *in vitro* assays, such as ELISPOT assays against CEF (Influenza, CMV, and EBV) peptide pools. Up to 32 ml of blood will be obtained from all eligible patients at the designated time points in 8 ml CPT tubes. PBMC will be processed by standard laboratory procedures, transferred to cryogenic vials, and stored in a liquid nitrogen freezer until further analysis. Please see the Laboratory Manual for further details.

### **9.2 Serum Studies**

Baseline and post-treatment sera will be collected to identify potential therapeutic targets, biomarkers, and predictors of response. Serology analysis for cytokine production by PBMC will be evaluated using the human serum cytokine multiplex approach that can test for up to 27 different cytokines (IL-1b, IL-1ra, IL-2, IL-4, IL-5, IL-6, IL-7, IL-8, IL-9, IL-

10, IL-12(p70), IL-13, IL-15, IL-17, eotaxin, basic FGF, G-CSF, GM-CSF, IFN $\gamma$ , IP-10, MCP-1, MIP1a, MIP1b, PDGF-BB, VEGF, TNF $\alpha$ , and TGF $\beta$ ). Whole blood (up to 10 ml) will be collected in a 10 milliliter Serum Separator Tube (SST tube) at the designated time points. Aliquots of 1 ml of serum will be transferred to cryogenic vials and stored at -80°C or below. Please see the Laboratory Manual for further details.

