### **1.3 Exploratory Objectives**

- 1.3.1 To estimate progression-free survival (PFS) and time to progression (TTP) in patients treated with Helixor® M mistletoe extract using RECIST 1.1 and irRC.
- 1.3.2 To collect peripheral blood mononuclear cells (PBMCs), serum, and plasma to explore potential therapeutic targets, biomarkers, and predictors of treatment response (PFS and best overall response).
- 1.3.3 To assess tumor burden dynamics using exploratory circulating biomarkers in serial collections of sera and plasma at baseline and throughout treatment.
- 1.3.4 To collect pre and post-treatment whole blood to evaluate germline mutations in circulating DNA that may correlate with clinical benefit (PFS and best overall response).
- 1.3.5 To determine changes in cytokine production by peripheral blood mononuclear cells (PBMC) as indicated by interleukin 2 [IL-2], interleukin 6 [IL-6], interleukin 8 [IL-8], interleukin 12 [IL-12], and interferon- gamma [IFN-γ].

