Exploratory objectives will be to 1) to estimate PFS and TTP in patients treated with Helixor® M at MTD or maximum administered dose if no MTD is determined, and to measure tumor marker dynamics in patients receiving treatment, 2) collect peripheral blood mononuclear cells (PBMCs) and serum to explore potential therapeutic targets, biomarkers, and predictors of treatment response, 3) assess tumor burden dynamics using exploratory circulating biomarkers in serial collections of sera and plasma at baseline and throughout treatment, 4) collect pre and post-treatment whole blood to evaluate germline mutations in circulating DNA that may correlate with clinical benefit, and 5) determine changes in cytokine production by peripheral blood mononuclear cells (PBMC) as indicated by interleukin 2 [IL-2], interleukin 6 [IL-6], interleukin 8 [IL-8], interleukin 12 [IL-12], and interferon- gamma [IFN-γ]. PFS and TTP will be analyzed as time-to-event outcomes, for which we can estimate event-time distributions using the Kaplan-Meier method. PFS will be calculated as the time from start of treatment to time of progression per RECIST 1.1 and irRC or death, whichever occurs first. If the subject does not have a documented date of progression or death, PFS will be censored at the date of the last adequate assessment. Patients who start any subsequent anti-cancer therapy without a prior reported progression will be censored at the last evaluable tumor assessment prior to initiation of the subsequent anti-cancer therapy. TTP is the time from start of treatment to time of progression per RECIST 1.1 and irRC.

We will examine the correlation between potential therapeutic targets/biomarkers/predictors of treatment response and clinical endpoints. For time-to-event clinical endpoints, the potential predictors will be treated as covariates (time-varying or not) in Cox proportional-hazard models. For other clinical endpoints, we will use generalized estimating equations (GEE) to analyze the correlation between the potential predictors and clinical endpoints. Summary statistics and boxplots will be used to present the levels of potential predictors at each time point, assess tumor burden dynamics, compare pre and post-treatment germline mutations in circulating DNA, and examine the changes in cytokine production by PBMC.

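### The cytokine objective is worded as production by PBMC, but the assay assigned to it measures serum concentration, which cannot show that PBMC are the source

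*Protocol*

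**What the plan says.** Protocol Section 1.3, objective 1.3.5, reads: "To determine changes in cytokine production by peripheral blood mononuclear cells (PBMC) as indicated by interleukin 2 [IL-2], interleukin 6 [IL-6"; the list continues with IL-8, IL-12 and IFN-gamma. Section 13.3 repeats this as the fifth exploratory objective and plans summary statistics and boxplots to "examine the changes in cytokine production by PBMC".

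Section 9.2 names the assay: "Serology analysis for cytokine production by PBMC will be evaluated using the human serum cytokine multiplex approach". The specimen is serum from a separator tube: "Aliquots of 1 ml of serum will be transferred to cryogenic vials and stored at -80°C or below".

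Section 9.1 deals with the cells themselves: "Baseline and post-treatment PBMC will be collected to monitor peripheral immunologic changes in response to therapy". They are frozen for later in vitro work, "such as ELISPOT assays against CEF (Influenza, CMV, and EBV) peptide pools". That section does not mention the five cytokines of 1.3.5. Sections 9.1 and 9.2 both leave further detail to a Laboratory Manual.

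In the study calendar (Section 10), the PBMC and serum rows carry the same marks: the Mondays of Weeks 1, 4, 8 and 12, a mark at about Week 16, and the off-study visit. Neither these rows nor the plasma row says whether the draw comes before or after the infusion.

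**The concern.** The objective names a cell-level quantity: how much cytokine PBMC make, and whether treatment changes it. The assay assigned to it gives a different quantity, the concentration circulating in serum. PBMC contribute to that concentration, but so may tumour, vessel wall, liver, tissue macrophages and any intercurrent infection, and clearance acts on the total. In patients with advanced solid tumours, progression or infection during follow-up could move a serum cytokine with no change in what PBMC produce.

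At stake is the statement the trial could make. An analyst following 1.3.5, 9.2 and 13.3 literally would report a change, or no change, in PBMC cytokine production from data that cannot identify the producing cell.

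**Working it through.** The protocol gives no sample size, power, error rate or effect size for this objective, and the point needs none. The check is a comparison of sections.

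1. **Quantity to be estimated.** In 1.3.5 and 13.3 it is the change in cytokine production by PBMC, for five named cytokines.
2. **Assay linked to it.** Section 9.2 is the only place where the protocol ties an assay to PBMC cytokine production, and the assay is a serum multiplex.
3. **Panel.** The list in 9.2 has 27 entries, which agrees with its stated maximum of 27. All five cytokines of 1.3.5 are on it (IL-12 as p70). Coverage is therefore not the problem; the specimen is.
4. **Specimen handling.** Section 9.2 goes from serum tube to 1 ml aliquots to the freezer. It has no step in which PBMC are cultured or stimulated, and no supernatant is assayed.
5. **Cells.** PBMC are collected at the same calendar marks as serum. The one assay named is ELISPOT against influenza, CMV and EBV peptide pools. The phrase introducing it leaves the list open, but nothing there is tied to the five cytokines.
6. **Inference.** For each cytokine, serum level = (release from PBMC + release from all other sources) − clearance. One serum value per visit does not separate these terms, so a change in the total does not identify a change in the first term.

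**Timing, checked separately.** With Week 1 Monday as day 1, Week 4 Monday is day 22, and 3 weeks × 3 infusions = 9 scheduled infusions come before it (1 lead-in and 8 at the assigned dose). The Friday of Week 3 is day 19, so a pre-dose draw on day 22 falls 22 − 19 = 3 days, or about 72 hours, after the last infusion. This interval is only nominal. The Monday visit has a +2 day window, one treatment a week may move by a day, and the calendar does not fix the draw relative to that day's infusion. Step 6 holds whatever the day of the draw, so timing is not the source of the mismatch.

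**The case against.** The strongest reply is that the planned collection is wider than the serum assay. PBMC are drawn serially, stored in liquid nitrogen and intended for in vitro work, with ELISPOT given only as an example. ELISPOT is itself a cell-based secretion assay, and the Laboratory Manual, which is not at hand, may say more. This stands in part: a reader might infer that objective 1.3.5 cannot be answered at all, and the documents do not support that. The limit applies to the serum multiplex. It does not remove the mismatch, because the protocol expressly assigns PBMC cytokine production to serum and names no cell-based assay for the five cytokines.

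Three other stronger readings also fail.

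- **That a flat result would be uninformative because the samples come too late after dosing.** The protocol gives no cytokine kinetics. The 24-hour text in Section 5.4 is an exception to the DLT definition, not a statement of how long reactions last; Section 5.5 allows for fever beyond 3 days and for hypersensitivity symptoms within a week. The reading also assumes pre-dose draws, which the calendar does not specify. Looking for sustained change before the week's first dose is a legitimate choice.
- **That the baseline sample might follow the first infusion.** Sections 9.1 to 9.3 each call for baseline samples, and no research draw is scheduled earlier than Week 1 Monday. Baseline in its plain sense is before dosing.
- **That serum cytokines would be invalid as predictors of PFS or response.** A circulating level can be examined as a predictor whatever cell released it. Objective 1.3.2 and the opening of Section 9.2 plan this separately.

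**Conclusion.** The point holds as a mismatch between objective and assay. Sections 1.3.5 and 13.3 state a PBMC-specific quantity, Section 9.2 measures a circulating one, and the second cannot be attributed to the first. All five named cytokines are affected.

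The consequence is limited. The objective is exploratory, the planned summary of cytokine changes is descriptive, and no dose, safety or primary conclusion rests on it. What changes is the conclusion that can be drawn: a change in serum concentration is supportable from the assay as described, and a change in PBMC production is not.

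This rests on one general premise, that serum cytokines do not come from PBMC alone, and on the protocol text as it stands. If the Laboratory Manual already specifies a PBMC-based assay for these five cytokines, the protocol wording would still need to be brought into line with it.

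**What to change.** Choose one of two routes and apply it in 1.3.5, 9.2 and 13.3 together.

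- **If the circulating level is what is wanted:** restate the endpoint as *change in serum cytokine concentrations (IL-2, IL-6, IL-8, IL-12, IFN-gamma)* and remove the reference to production by PBMC. This costs wording only.
- **If PBMC production is what is wanted:** keep the objective and assign the five-cytokine read-out, in Section 9.1, to a named in vitro assay on the PBMC already collected and stored. Section 9.2 would then describe serum cytokines as a separate measurement. This needs no new blood draw; the cost is some extra laboratory work.

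As a minor clarification under either route, add a calendar footnote to the PBMC, serum and plasma rows saying that samples are drawn before that day's infusion. This makes explicit what the word baseline already implies for Week 1 and keeps later draws comparable across sites. It too costs wording only. No change to the sampling days is needed for this point.
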